### Outcome

All outcome measures will be structured as web‐based questionnaires and sent to the participants' email addresses at baseline, post‐intervention (5 weeks follow‐up), 3 months follow‐up, and 6 months follow‐up. To promote participant retention and follow‐up completion, monthly email reminders will be sent from the start of the intervention until the end of the follow‐up period. Any deviations from the trial intervention will be recorded during follow‐up assessments.

The primary outcome will be the GARS used to measure the severity of clinical symptoms and rate anxiety/fear and avoidance of gaze. The GARS comprises 17 items regarding social situations involving focused gaze.^3^ For each item, participants will rate the degree of anxiety/fear and the frequency of avoidance on a scale from 0 (“no anxiety” or “no avoidance”) to 3 (“a lot of anxiety” or “avoid a lot”). The total GARS score ranges from 0 to 102, with higher scores indicating a greater severity of gaze anxiety. The validity and reliability of the GARS have been demonstrated in the original English and German versions.^3^, ^17^, ^18^ The Japanese version of the Gaze Anxiety Rating Scale (GARS‐j) was developed through translation into Japanese by the first author ([name]) and back‐translation by the second author ([name]), with the resulting text being reviewed by the original scale developers (please refer to the GARS‐j in the Supporting Information).^19^ Furthermore, the validity of the GARS‐j will be examined using baseline responses from this trial. Table 3 shows secondary outcomes.

**Table 3 pcn570236-tbl-0003:** Secondary outcomes.

Outcome	Description
LSAS‐j	The LSAS‐j includes 24 social situations related to “fear or anxiety” and “avoidance,” which participants rank on a 4‐point scale (0 = never, 4 = severe), has a total score range of 0–144.^20^ The Japanese version of the LSAS has demonstrated reliability and validity and is widely used in Japanese clinical and research settings.^21^ Therapeutic response will be defined as a ≥28% decrease in the LSAS total score.^22^ Remission will be defined as an LSAS total score of <35,^23^ consistent with a previous RCT.^10^ Conversely, worsening will be defined as a ≥28% increase in LSAS total score to assess the risk of exacerbating social anxiety.

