### Sample size

The sample size for this study was set at 249 (Figure 1), considering the following G*Power estimated values and a 20% attrition rate (version 3.1.9.7; The G*Power Team).^30^, ^31^ We set the parameters for the *F* tests—anova: fixed effects, omnibus, one‐way, with an effect size *F* = 0.25 (medium), an *α* error probability of 0.05, and a power (1 − *β* error probability) of 0.9 for three groups. These inputs yielded a noncentrality parameter of 12.94, a critical *F* of 3.04, an original total sample size of 207, and an actual power of 0.902.

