### Randomization

Eligible participants will be randomly assigned to each group at a ratio of 1:1:1, with assignments made using a block randomization method with R' “randomizr” package,^32^ ensuring a balance in baseline Japanese version of the Liebowitz Social Anxiety Scale (LSAS‐j) total scores of <50 or ≥50, sex (male or female), and facilities as adjustment factors. Allocation by using the randomizer will be conducted by the second author ([name]). The randomization sequence will be concealed from researchers at each university, and the statistician will remain blinded to participants' group assignments.

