### Statistical analysis plan

Statistical analyses will be performed by the second author ([name]) using IBM spss Statistics (IBM Corp., Armonk, NY, USA) and will adhere to the intention‐to‐treat principle. The analyst was not involved in creating the two intervention programs. The analyst will be concealed to group allocation when accessing the data. This means she will not know which specific intervention a group received or if each participant was in the control condition.

Descriptive statistics will be used to summarize demographic data (including participants' age and sex) and the severity of clinical symptoms on each scale. Group differences will be compared to determine statistical significance. As a primary analysis, mixed‐effects models will examine significant differences in the mean change in total scores on each symptom rating scale between the groups from baseline to Week 5 (1 month), Week 13 (3 months), and Week 26 (6 months) post‐intervention. If an overall significant difference is found, multiple comparisons will be conducted. For multiple comparisons, we will implement Dunnett's test to control for inflated Type I error rates.^33^ Effect sizes will be calculated between and within the groups. The significance level for hypothesis testing will be set at a two‐tailed *α* of 0.05, and 95% two‐sided confidence intervals will be calculated.

For the binary variables of treatment response, remission, and worsening, the odds and risk ratios between the groups will be analyzed using Fisher's exact test. To further evaluate the risk of worsening social anxiety, as measured by the LSAS, we will calculate the risk ratio, relative risk reduction, absolute risk reduction, and number needed to treat.

We plan to conduct a sensitivity analysis excluding participants with insufficient engagement in the self‐help intervention and those who provided implausible response patterns—specifically, patterns like straight‐lining, contradictory responses, or inconsistent responses between the GARS‐j and the LSAS‐j. Participants will be defined as having sufficient engagement if those in the self‐help book group have completed at least two chapters, and those in the ICBT group have reached the “Behavioral Experiments” treatment module. The sensitivity analysis, similar to the primary analysis, will be performed after imputing missing values using R's “mice” package.^34^

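### The Fisher's exact test named for response, remission and worsening yields no risk ratio and ignores the baseline LSAS-j randomisation factor, which costs power on secondary outcomes

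*Protocol article*

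**What the plan says.** Statistical analysis plan: "For the binary variables of treatment response, remission, and worsening", the plan states that "the odds and risk ratios between the groups will be analyzed using" Fisher's exact test. No stratum or covariate is named. For worsening alone, the next sentence adds that "we will calculate the risk ratio, relative risk reduction, absolute risk reduction, and number needed to treat".

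Outcome, Table 3: all three variables come from the LSAS-j total. Response is a 28% or greater "decrease in the LSAS total score", worsening is a rise of the same relative size, and remission is an absolute total below 35.

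Randomization: allocation is balanced on baseline LSAS-j total (<50 or ≥50), "sex (male or female), and facilities as adjustment factors".

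Statistical analysis plan, on the analysis set: the analyses "will adhere to the intention‐to‐treat principle". Sample size: the target of 249 allows for "a 20% attrition rate".

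**The concern.** Two things do not fit together.

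- **Estimand and method.** The plan promises risk ratios but names a test that does not produce them. For response and remission, the article gives no other route to a risk ratio and its confidence interval.
- **Design and analysis.** The trial balances on baseline LSAS-j, then tests outcomes built from the same scale in a table that pools over that factor. For remission the link is structural. The inclusion criteria set a floor on the GARS but none on the LSAS-j, so a participant can enter already below 35, and every such participant is in the <50 stratum.

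The Discussion counts these categorical outcomes among the trial's strengths because they are clinically meaningful. If they are tested with a method that is conservative at this sample size, a real benefit in remission or a real excess of worsening is easier to miss.

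**Working it through.** **Inputs from the protocol.** N = 249, allocation 1:1:1, 20% attrition, two-sided α = 0.05, and the LSAS-j definitions above. Event rates are not given, so those below are assumptions shown as a range. Tests are taken as pairwise, each active arm against control.

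**The plan's own figure.** The only stated calculation is for the one-way ANOVA. With f = 0.25 and N = 207, λ = 207 × 0.25² = 12.94, the critical F on 2 and 204 df is 3.04, and power is 0.902. All three figures reproduce. No figure is stated for the binary outcomes. The number per arm used here is 249 × 0.8 / 3 = 66.4, taken as 66.

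**Step 1: what Fisher's test delivers.** Take 42/83 v 25/83 events as an illustration. Fisher's test gives p = 0.011 and a conditional odds ratio of 2.36 (95% CI 1.20 to 4.73). The risk ratio is (42/83)/(25/83) = 42/25 = 1.68. It has to be calculated separately, with its own interval.

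**Step 2: true size at 66 v 66.** Sum the binomial probabilities of all tables with Fisher p ≤ 0.05 when both arms share event rate p:

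| Event rate p | True size at nominal 0.05 |
|---|---|
| 5% | 0.012 |
| 10% | 0.024 |
| 20% | 0.031 |
| 30% | 0.032 |
| 50% | 0.030 |

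**Step 3: power with and without stratification.** Assume two LSAS-j strata of equal size (33 per stratum per arm) and a common odds ratio of 2.5. Active rates follow from odds × 2.5. For example, 60% gives 1.5 × 2.5 = 3.75, so 3.75/4.75 = 78.9%; 10% gives 0.111 × 2.5 = 0.278, so 0.278/1.278 = 21.7%. Simulated trials were analysed by Fisher's test on the pooled table and by Cochran-Mantel-Haenszel (CMH, no continuity correction) stratified on LSAS-j:

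| Control rate, low / high LSAS-j | Size, Fisher v CMH | Power at OR 2.5, Fisher v CMH |
|---|---|---|
| 60% / 10% (strong) | 0.013 v 0.048 | 0.33 v 0.57 |
| 50% / 20% (moderate) | 0.026 v 0.053 | 0.56 v 0.69 |
| 30% / 30% (none) | 0.033 v 0.050 | 0.66 v 0.72 |

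Repeat runs put the Fisher power in the first row at 0.32 to 0.33, which is simulation error.

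**Reading the table.** With no stratum effect the gap is 0.72 − 0.66 = 0.06, which reflects only the conservatism of the exact test. With a moderate effect it is 0.69 − 0.56 = 0.13, and with a strong one 0.57 − 0.33 = 0.24. The growth beyond 0.06 comes from ignoring a prognostic factor on which the arms are balanced. The stratified test keeps its size near 5% throughout.

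**The case against.** The case for leaving the plan alone has several parts.

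- **The wording is loose but the meaning is clear.** A natural reading is that ratios are computed from the 2×2 table and Fisher's test supplies the p-value. The section also promises 95% confidence intervals in general, and unadjusted risk ratios are legitimate under randomisation. This stands in part: the remedy for the first half of the point is mostly wording. For worsening, risk measures are explicitly planned, so it cannot be said that the plan leaves worsening without a risk ratio.
- **The stratum may not matter.** No rates are given. Response and worsening are percentage changes from each participant's own baseline, so their dependence on the LSAS-j stratum is uncertain. This stands. The strong scenario is plausible chiefly for remission, and the gain shrinks to about 6 points of power if there is no stratum effect.
- **These are secondary outcomes and the test errs on the safe side.** This also stands. The trial is not sized on them, the GARS mixed model is untouched, and adverse events are collected separately.

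A reader might also infer that the binary analyses use only those who answer, and so depart from intention to treat. The article does not say so. It states the intention-to-treat principle and is silent on how a missing LSAS-j is classed, a detail that a condensed article commonly leaves to the full plan. Imputation with mice is described for the sensitivity analysis, but the phrase likening that analysis to the primary one leaves its scope open. Nor does Fisher's test require complete cases. With 33/66 v 20/66 observed, p = 0.033; with the 17 missing per arm classed as non-events, 33/83 v 20/83 gives p = 0.045.

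**Conclusion.** The point holds as one of precision and efficiency on secondary outcomes. The named test does not give the risk ratios that the plan promises for response and remission, and it leaves out the baseline LSAS-j factor that the randomisation uses.

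The conservatism (true size 0.012 to 0.032 at 66 per arm) does not depend on any stratum effect. For worsening, if events are as rare as 5%, the nominal 5% test runs at about 1.2%. The power loss at an odds ratio of 2.5 ranges from about 6 to 24 percentage points. It rests on the assumed control rates, equal strata and a common odds ratio, none of which the protocol supplies. The upper end should be read as applying to remission if the stratum effect is strong.

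Three stronger conclusions are not supported: that false positives are inflated, that baseline LSAS-j has been shown to drive all three outcomes, and that the binary analysis is complete-case or breaches intention to treat.

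**What to change.** Replace the Fisher sentence with a method that yields the promised measures and uses the randomisation factor:

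- For each binary outcome, compare each active arm with control by Mantel-Haenszel stratified on baseline LSAS-j (<50 or ≥50), or by logistic regression adjusted for baseline LSAS-j with standardised risks.
- Report risk ratios and risk differences with 95% confidence intervals for response and remission as well as worsening.
- Keep Fisher's test as a supportive check when events are sparse.
- Where LSAS-j is missing, the mice imputation already planned can be applied to the LSAS-j total before the binary status is derived. One sentence stating the rule would remove the ambiguity.

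Stratifying on all three randomisation factors is not advisable: 2 × 2 × 12 facilities = 48 cells for 249 participants, about 5 each.

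The cost is a change of wording and slightly more analysis, with no new data. The one drawback is that a regression model needs enough events. Mantel-Haenszel on two strata is the simpler choice when they are few.

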## DISCUSSION

The limitations of this study include the inability to determine the true effects of the two self‐help CBT programs because the control is not a placebo (sham treatment). Because recruitment for this study will take place at universities affiliated with researchers specializing in CBT, many potential participants will have a clinical psychology background and may be able to discern the researchers' intentions if an attention control or psychoeducation condition is used as a placebo. This is because the lectures will have explained that CBT is an effective treatment for SAD, and they can find out through an internet search that CBT for SAD is covered by insurance in Japan. On the other hand, a no‐treatment control group could lead participants to seek treatment outside the study, including face‐to‐face CBT, during the observation period. Furthermore, disappointed participants might withdraw from the study, which could increase the risk of bias. Given these practical constraints, we believe it is more appropriate for the control group to be guaranteed an intervention (self‐book CBT) after the study.

Another potential limitation is that the outcomes are self‐rated psychological scales; therefore, the potential influence of positive expectations resulting from the intervention on the outcomes cannot be excluded.^35^ Self‐report outcomes may be susceptible to bias due to reliance on respondents' subjectivity and memory. The protocol mitigates this by employing outcomes comprising specific, behaviorally anchored questions (e.g., the GARS‐j and the LSAS‐j), which clearly define the timeframe and frequency of symptoms and aim to facilitate participants' accurate reporting of their actual symptoms. To minimize recall bias, links to the online questionnaires will be promptly emailed to participants at each assessment point. The online format of responses may also reduce socially desirable responses compared with in‐person assessments.^36^ This may encourage participants to report their actual clinical symptoms without hesitation.

This trial excludes participants with a formal diagnosis of SAD during screening. Consequently, the evidence presented will pertain to a non‐clinical population (young adults at high risk), which will limit its generalizability to clinical settings. The efficacy of those interventions for gaze anxiety in individuals already diagnosed with SAD should therefore be verified in a clinical setting.

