This trial protocol has several strengths. Outcomes will be assessed not only post‐intervention but also at the 6‐month follow‐up, which should enhance the estimation of true effectiveness. The ITT principle allows for the derivation of unbiased conclusions regarding the effectiveness of the intervention.^37^ The sensitivity analyses could show the robustness of the results from the primary analysis.^38^ The statistical analysis plan will evaluate both continuous outcome data and clinically meaningful categorical variables (treatment response, remission, and worsening). Furthermore, the multisite design across numerous Japanese research institutions aims to achieve an adequate sample size and mitigate selection and facility biases.

This trial protocol was designed to investigate the efficacy of self‐help CBT programs on gaze and social anxiety in young adults. Despite some limitations, the multiple strengths could yield novel evidence.

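### The sensitivity analysis drops low-engagers from the two active arms only, so it is a per-protocol-type comparison that cannot show the intention-to-treat result is robust

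*Protocol article*

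**What the plan says.** Under Statistical analysis plan, the article states that the analyses "will adhere to the intention‐to‐treat principle". It then describes one sensitivity analysis, "excluding participants with insufficient engagement in the self‐help intervention" and also removing implausible response patterns.

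- **Book arm:** "Participants will be defined as having sufficient engagement if those in the self‐help book group have completed at least two chapters".
- **ICBT arm:** engagement is sufficient when "those in the ICBT group have reached the “Behavioral Experiments” treatment module".
- **Control arm:** no criterion is given. The Control group section says this arm gets no active intervention.
- **Response patterns:** besides straight-lining, the grounds for exclusion include "contradictory responses, or inconsistent responses between the GARS‐j and the LSAS‐j". The GARS is the primary outcome and the LSAS-j is a secondary one. No time point is attached to the rule.
- **Missing data:** values are imputed with the R package mice before this analysis, which is described as similar to the primary one.

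Among the trial's strengths, the Discussion says: "The sensitivity analyses could show the robustness of the results from the primary analysis". On the no-treatment control, it also acknowledges that "disappointed participants might withdraw from the study, which could increase the risk of bias".

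**The concern.** Engagement is observed after randomisation and only two of the three arms can fail it. Excluding on it leaves the more persistent part of each active arm against the whole control arm, so the groups are no longer comparable by design. People who keep going with a self-help programme may differ in motivation or prognosis from those who stop, and that difference would be counted as treatment effect.

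Two further features make the result harder to read. The two engagement rules ask for different amounts of therapy. One data-quality rule depends on the primary outcome, which treatment can change if the rule is applied at follow-up.

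What is at stake is the use made of the result. If this analysis agrees with the primary one, the Discussion's wording invites a claim of robustness that the comparison cannot support. If it looks better than the primary one, selection alone could be the reason.

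**Working it through.** **The plan's own figure.** The Sample size section gives N = 207 for three groups with f = 0.25, alpha 0.05 and power 0.90. This reproduces: noncentrality 207 × 0.25² = 12.94, critical F 3.04, power 0.902. The point does not turn on it, but it supplies a scale. If both active arms are equally better than control (an assumption; the article gives only f), the standard deviation of the three means is d × √2/3, so d = 0.25 × 3/√2 = 0.53 SD.

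**Thresholds side by side (Tables 1 and 2).**

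| | Book | ICBT |
|---|---|---|
| Rule | 2 of 5 chapters completed | module 5 of 10 reached |
| Share by unit count | 2/5 = 40% | 4/10 = 40% done (5/10 = 50% if module 5 must be finished) |
| Share by volume | (31 + 21)/191 = 52/191 = 27% of tabulated pages | 40% to 50% of modules |
| Approximate time | 150 × 52/191 = 41 min | 4 × 15 = 60 to 5 × 15 = 75 min |
| Scheduled week | 2 | 5 |
| Content covered | psychoeducation and the cognitive behavioural model | these plus safety behaviours, video feedback and attention training |

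The book's techniques, including behavioural experiments, start in chapter 3. A book reader can therefore qualify without opening the technique chapter, while an ICBT user cannot qualify without passing three technique modules. The Adherence section adds a difference in measurement: chapters read are self-reported at the initial outcome assessment, whereas ICBT modules are logged automatically.

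**Size of the selection effect with no true treatment effect.** The article gives neither the correlation between engagement and improvement (ρ) nor the share excluded (q), so both are assumptions. Take engagement and improvement as bivariate normal and drop the lowest q of an active arm. With c = Φ⁻¹(q) and λ = φ(c)/(1 − q), the retained mean shifts by

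bias = ρ × λ (in SD units).

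Example: ρ = 0.3 and q = 30% give c = −0.524, λ = 0.348/0.7 = 0.497, and bias 0.3 × 0.497 = 0.149 SD.

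For the type I error, take 249/3 = 83 per arm, all controls kept and 83(1 − q) active participants kept. The retained variance is 1 − ρ²λ(λ − c), and the test is a two-sided 0.05 normal test of one active arm against control, before the Dunnett adjustment.

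| ρ | q = 10% | q = 30% | q = 50% |
|---|---|---|---|
| 0 | 0 SD (5.0%) | 0 SD (5.0%) | 0 SD (5.0%) |
| 0.1 | 0.02 SD (5.2%) | 0.05 SD (6.0%) | 0.08 SD (7.0%) |
| 0.2 | 0.04 SD (5.7%) | 0.10 SD (9.0%) | 0.16 SD (13.5%) |
| 0.3 | 0.06 SD (6.6%) | 0.15 SD (14.3%) | 0.24 SD (25.0%) |

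Against the 0.53 SD scale, the middle case at ρ = 0.3 is 0.149/0.53 = 28% of the planning effect.

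**Unequal exclusion between the active arms.** If, as an illustration, 10% of the book arm and 40% of the ICBT arm are dropped, ICBT appears better than the book by 0.129 − 0.039 = 0.090 SD at ρ = 0.2 and by 0.193 − 0.058 = 0.135 SD at ρ = 0.3.

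**The GARS-j/LSAS-j rule.** It applies to all arms. Applied at baseline, it cannot be influenced by treatment. Applied at follow-up, it can: a programme that eases gaze anxiety more than general social anxiety could make true responders look inconsistent. The article does not say which is meant, and the direction of any bias cannot be derived from it.

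**The case against.** The strongest reply is that the consequence is limited. The primary analysis is intention-to-treat and untouched, and the Discussion is hedged, saying only what the sensitivity analyses could show. That stands, and it limits how serious the point is. It does not rescue the use: a comparison of a different, self-selected population does not test the primary result, however cautiously it is worded.

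Several stronger readings are tempting, and the article does not support them.

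- **That the analysis is certainly biased toward benefit.** This needs engagement to go with better outcome, and no figure is given. The bias is zero at zero correlation and reverses if people who improve early stop reading.
- **That the thresholds are unequal on every count.** By number of units they agree, 2 of 5 against 4 of 10. They differ by content, time and scheduled week.
- **That the inconsistency rule adds to a bias in favour of treatment.** Its direction is unknown, and it may be meant only as a baseline data-quality screen.
- **That imputation is used only together with the exclusions, so informative dropout is never examined.** Describing the analysis as similar to the primary one can equally mean that the primary analysis is imputed too. Further missing-data analyses may sit in a full analysis plan that is not shown. The article calls withdrawal by disappointed participants possible, does not predict it, and offers controls the book afterwards.
- **That the planned tests distort book against ICBT.** Standard Dunnett testing compares each arm with control. The distortion would reach that contrast only through the between-group effect sizes, and the exclusion shares used above are illustrative.

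**Conclusion.** The concern holds in limited form. As written, the only sensitivity analysis described is a per-protocol-type analysis with a post-randomisation exclusion that controls cannot fail. It is likely to favour the active arms, by about 0.02 to 0.24 SD under no true effect for assumed correlations of 0.1 to 0.3 and 10% to 50% excluded. Whatever the direction, it does not test the assumptions behind the intention-to-treat result and should not be cited as evidence of its robustness. The difference between thresholds in content and schedule, and an outcome-based exclusion with no time point, are secondary weaknesses of the same analysis. The size rests on the normal selection model and on assumed inputs. The structural conclusion rests only on the stated rules.

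**What to change.** 1. Relabel the engagement analysis as supplementary (per-protocol), and remove it from the Discussion as support for the robustness of the primary result.
2. Set the engagement threshold at the same component in both active arms: behavioural experiments, which is chapter 3 of the book and module 5 of ICBT. State for both whether the unit must be started or finished. The match is approximate, because chapter 3 also holds material that ICBT places in modules 6 to 8.
3. Limit response-quality exclusions to baseline data or to within-scale patterns, applied blind to arm.
4. As the sensitivity analysis of the intention-to-treat result, run the mice imputation on all randomised participants without exclusions, with a departure from missing at random that can differ by arm. State in the same sentence whether the primary analysis is also imputed.

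A complier-average estimate, with randomisation as the instrument, is optional only. It assumes no effect below the threshold, which is implausible for someone who has completed ICBT modules 1 to 4, and it would overstate the effect if those modules help.

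The cost is a little more analysis work with software and data already in the plan. The other downside is that fewer book participants will count as engaged.
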